**DOCUMENT HISTORY**

| **Version** | **Date** | **Summary of change** |
| --- | --- | --- |
| 1.0 | 5th August 2020 | Original |
| 1.1 | 18th November 2020 | SEES and audio recording of interview |
| 2.0 | 7th June 2023 | Change in research personnel and intervention |

**ABBREVIATIONS AND DEFINITIONS OF TERMS**

AEP – Accredited Exercise Physiologist

AIT – aerobic interval training

BPRS- Brief Psychiatric Rating Scale

PA – Physical activity

PI – Principal Investigator

RCT – Randomised Controlled Trial

RT- resistance training

SMI – Severe Mental Illness

SANS – Scale Assessment of Negative Symptoms

SIMPAQ – Simple Assessment of Physical Activity Questionnaire

# Introduction

Chronic psychotic disorders, such as schizophrenia and related psychoses are complex and typically start early in adult life. Whilst considered a low prevalence disorder (1), the impact of schizophrenia through reduced quality of life, lost productivity and reliance on carers and the health service, can be very large (2). People with chronic psychotic disorders can experience significant burden from active symptoms of their mental illness, leading to functional impairment, and associated disability, with median social and clinical recovery considered to be as low as 13.5% (3).

Psychotropic medications and psychosocial therapies can successfully result in a reduction in many symptoms of psychotic disorders, such as hallucinations, delusions and depression, however recovery can be hampered by treatment resistance, incomplete response and distressing side effects of medications. Some specific symptom domains (such as negative and cognitive symptoms) are common (4), do not respond well to psychotropic medications and can be exacerbated by the medications themselves, with no currently accepted effective pharmacotherapy for negative or cognitive symptoms of schizophrenia (5, 6).

Low cardiorespiratory fitness and muscular weakness contribute to the very poor physical functioning and health of people with chronic psychotic disorders (7-9) which is in turn, associated with reduced global functioning (10). There is an urgent need to develop effective treatments that may augment existing first line treatments and improve functioning and recovery rates for people with chronic psychotic disorders.

In recent years, there has been increasing focus on the use of exercise interventions for people with chronic psychotic disorders, not only to improve the physical health of this population (11) but also as a strategy to improve mental health outcomes, with a growing evidence base regarding the positive impact of exercise on symptoms and functional outcomes (positive symptoms, negative symptoms, quality of life, functioning), (12, 13).

However, the vast majority of these interventions have investigated aerobic exercise protocols (13, 14) (defined as “exercise that uses oxygen to meet energy demands via aerobic metabolism to increase cardiorespiratory fitness”) or aerobic in combination with resistance training elements (resistance training defined as “repeated muscular movement that may increase muscle strength”), (15).

A 2015 meta-analysis found that exercise interventions above 90 mins of moderate to vigorous exercise per week was shown to improve positive, negative and mood symptoms in people with schizophrenia (13), although most of these trials involved continuous aerobic training. Scant attention has been paid to resistance training (RT) as a stand-alone treatment, identified as a significant gap in the literature and our understanding of the impact of this type of training in people with schizophrenia and psychotic disorders (16, 17).

In the general population hand grip strength (as a proxy measure of muscular strength) has been found to be inversely associated with mortality and may in fact be a better predictor of mortality than other conditions known to impact health such as hypertension or diabetes (18, 19). RT in the general population has resulted in improvements in both muscular performance and strength, with improvements also seen in chronic health conditions such as diabetes, cardiovascular disease, hypertension and metabolic abnormalities (20).

In clinical mental health populations such as people with depressive and anxiety disorders, there appears to be mounting evidence of improvements in mood, both in stand- alone RT and combination with aerobic interventions (21). In a large cross-sectional study involving people with schizophrenia, hand grip strength was found to be associated with cognitive outcomes such as working memory and processing speed (19). Preliminary evidence involving a small number of studies indicates the potential feasibility and safety of RT in this population (22,23), and that some people with schizophrenia may in fact express a preference for this type of training (24,25). A small number of trials have revealed the potential for physical health improvements such as power, strength and walking efficiency, which has promise given the potential impact of functional improvement on independent daily living tasks which can be challenging for people with chronic psychotic disorders (14, 22, 23, 26).

Further, only two randomised controlled trials have examined the impact of stand- alone RT on mental health outcomes, with conflicting results with respect to mental health symptoms, global functioning and quality of life (22, 23). Current recommendations for RT in people with psychotic disorders are derived from general population guidelines regarding physical health benefits of RT ie resistance training of main muscle groups at least two times per week. Whilst research regarding the impact of RT in depression and anxiety has revealed mental health benefits, few definitive conclusions can be drawn regarding about the impact of RT on mental health outcomes in people with psychotic disorders at this stage.

Another gap in the literature is that very few studies in people with chronic psychotic disorders have compared types of exercise with each other (27), with the majority of evidence regarding the benefits of exercise being derived from trials in which aerobic or combined aerobic and resistance exercise is compared with an inactive or non-exercise control. Specifically, few trials in people with schizophrenia have addressed comparisons between aerobic and resistance training protocols and those that have, have evaluated physical parameters such as brain volume or physical fitness, rather than mental health outcomes (28, 29).

Understanding the differential effects of resistance training versus aerobic exercise with respect to impact on functional and mental health outcomes is crucial to help guide optimal exercise prescription in this population and provide people with schizophrenia and related psychoses the best evidence regarding treatment options that may assist with recovery. Acknowledging the importance of enjoyment in long term adherence to exercise, of particular interest is whether this type of training can be enjoyed by people with psychotic disorders, as either complementary to, or as an alternative to more traditionally prescribed aerobic programs.

Community Care Units (CCU’s) are residential rehabilitation units for people with SMI (predominantly schizophrenia and related psychoses) offering 24-hour intensive multidisciplinary support (30) to people who are typically admitted with treatment resistance and functional disability (31). CCU’s aim to deliver evidence-based rehabilitation interventions that improve independent functioning across a range of health domains (32). Acknowledging the recent expansion of rehabilitation aims for people with schizophrenia to include physical health interventions; understanding the differential impact of exercise types on mental health and functional outcomes in rehabilitation settings is important (33, 34).

Previous research in residential rehabilitation settings revealed feasibility and improvements in functional fitness following implementation of a supervised exercise interval circuit program comprising aerobic interval training involving both aerobic, body weight and resistance elements (24). Overall program acceptability was high, with resistance elements being a preferred component by participants of that program.

# Objectives

Using an exploratory 8-week randomised, controlled trial; the primary objective in this study is to assess the feasibility and acceptability of stand-alone RT compared to control, aerobic interval training (AIT) for people with chronic psychotic disorders undergoing psychiatric rehabilitation.

## Primary Objectives

To assess the feasibility and acceptability of stand-alone RT compared to control, aerobic interval training(AIT) based on recruitment, retention and participation.

## Secondary Objectives

To determine if 8 weeks of stand-alone RT compared to control, (AIT) improves mental (functioning, mental health symptoms) and physical health outcomes

To investigate comparisons of psychological responses to a single session of exercise (week 3 and 8) between exercise conditions, RT and AIT

To correlate preference for exercise condition (RT or AIT) prior to randomisation with subsequent adherence.

# Study Design

This study will be conducted as a single blind exploratory randomised controlled trial. Participants will be randomised to a supervised resistance training (RT) program or a supervised moderate intensity aerobic interval intervention (AIT), matched for volume and intensity, with the aim to compare RT with AIT with respect to our primary outcome (feasibility) in people with chronic psychotic disorders undergoing psychiatric rehabilitation.

**Feasibility Criteria**

Recruitment – percentage of participants who consent to the study as a proportion of CCU residents who are referred from the three sites. Recruitment into exercise trials for people with SMI can be highly variable, however > 50% (majority) will be considered feasible.

Retention – the proportion of participants consenting to the trial who complete follow up assessments at 8 weeks as a proportion of the total number allocated in each condition. Feasibility will be defined as > 65% based on previous research (49).

Participation – the number of supervised exercise sessions attended by participants in each condition (RT and AIT group) as a proportion of total available sessions (3 sessions per week for 8 weeks - 24); feasibility will be defined by attendance at greater than 60% of sessions (15 sessions).

Participants will be evaluated at baseline and end point week 8. Total duration of the study will be 8 weeks. All outcome raters will be blind to outcome allocation, however blinding of participants to their exercise condition will not be possible.

# Study Population

Forty participants (50) undergoing psychiatric rehabilitation will be recruited through three Metro South Addiction and Mental Health Service Community Care Units (Logan, Coorparoo, Bayside).

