## Number of participants

The study will consist of a total of 50 participants.

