**7.1.5 Randomisation Procedure and blinding**

Participants will be randomised once written consent has been obtained and the baseline assessments have been completed.

Participants will be assigned a unique code that will be sent to an independent biostatistician for randomisation using a computer -generated sequence of numbers. Randomisation to either RT or MIIT condition, will occur in a 1:1 ratio, using block randomisation.

Once randomisation has occurred, participants will be notified of their group allocation by an independent staff member to ensure the research team remains blinded to allocation.

There will be no opportunity to change conditions once randomised, however if participants wish they may withdraw from the study and continue to exercise using the equipment and AEP at each CCU independently from the study. If withdrawal occurs, reasons for doing so will be recorded in the CRF. Following randomisation, participants will be asked whether they are happy with the condition they have been randomised to, and this will be recorded in the CRF.

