## Sample Size and Power

This study will be conducted as an exploratory RCT with feasibility as the primary outcome. Based on recruiting an adequate sample to assess the feasibility of the study with the resources available (63) we aim to recruit 50 participants assuming approximately 25 participants will be assigned to each intervention arm, based on previous exercise research within this setting – we anticipate 20% drop outs per exercise condition (49).

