## Statistical Analysis

Data analyses will be conducted using SPSS Statistics 24, (SPSS Inc, Chicago, Illinois) for the primary outcomes. Continuous variables were summarized using means and standard deviations (SD) (or median and interquartile range for non-parametric data). All variables will be tested for normality using the Shapiro-wilks test, and visual inspection of Q-Q plots. Baseline demographic and clinical variables, participation and AE rates and mean aggregate acceptability scores will be compared between the two exercise groups using independent t-tests or Mann-Whitney U for non-parametric data. Chi square analysis for categorical data will be used to detect any baseline differences between the two exercise groups and for comparison of acceptability categories (strongly agree/agree versus other) per questionnaire item between the groups.

Baseline demographic and clinical variables will be compared between the 2 exercise groups using independent t tests (or Mann Whitney U tests if data non parametric) for continuous data and Chi2 square analysis for categorical data to detect any baseline differences between the 2 exercise groups. Baseline characteristics of those who complete >50% of the program will be compared to those who withdraw to identify characteristics of those who drop out.

To analyse the impact of the proposed exercise intervention on secondary outcomes, analyses will be performed on an intention-to-treat basis. Change from baseline in secondary outcomes at week 8 will be calculated as least squares (LS) means using a Linear Mixed Effects Model (LMM). Treatment group (RT or AIT) and time will be used as factors, with covariates established in previous similar research (age, gender, participation, and antipsychotic medication use),(García-Garcés et al., 2021b). Where group/time differences were detected, posthoc (Bonferroni) analyses will be carried out separately for the intervention and control group, with Cohen’s d estimate of effect sizes provided. LMM was performed using R (software version 4.04, 2024). All the statistical tests were two-tailed with the critical P value for significance set at?<?0.05.

For the RT group only, 12 RM strength will be assessed for normality and compared pre and post the intervention using paired samples t test.

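### Section 4 says forty participants will be recruited, which contradicts the target of 50 in sections 4.1 and 11.3

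*Protocol*

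**What the plan says.** The Protocol gives the number of participants in three places.

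- Section 4 (Study Population): "Forty participants (50) undergoing psychiatric rehabilitation will be recruited", through three Community Care Units.
- Section 4.1 (Number of participants), directly below: "The study will consist of a total of 50 participants".
- Section 11.3 (Sample Size and Power): "we aim to recruit 50 participants assuming approximately 25 participants will be assigned to each intervention arm".

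Three other statements bear on the consequence. Section 11.3 adds that "we anticipate 20% drop outs per exercise condition (49"), where 49 is a reference number. Section 7.1.5 says that allocation "will occur in a 1:1 ratio, using block randomisation". The Feasibility Criteria in section 3 define retention, within each condition, as the proportion of those allocated who complete the week-8 assessments: "Feasibility will be defined as > 65% based on previous research (49").

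No power calculation lies behind the target. Section 11.3 rests it on feasibility and resources: "Based on recruiting an adequate sample to assess the feasibility of the study with the resources available (63").

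**The concern.** Sections 4, 4.1 and 11.3 all speak of people entering the study, and one of them gives a different number from the other two. All three are operative text, so this is not a leftover in an amendment log.

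Feasibility is the primary outcome, and retention is one of its three criteria. Retention is judged in each arm against the number allocated, so the recruitment target sets the denominator of a primary criterion. It also sets how many people can be expected to supply week-8 data for the secondary outcomes. A trial that closed at 40 would satisfy the words of section 4 and fall short of sections 4.1 and 11.3. A later reader could not tell from section 4 whether the target had been met.

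**Working it through.** **Inputs**

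- Recruited: 40 in words (section 4); 50 (sections 4.1 and 11.3).
- Per arm: about 25 (section 11.3), with 1:1 allocation (section 7.1.5).
- Anticipated drop-out: 20% per arm (section 11.3).
- Retention criterion: more than 65% of those allocated, per arm (section 3).

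**1. The plan's own figure.** 2 × 25 = 50, so section 11.3 agrees with itself and with section 4.1.

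**2. How 40 and 50 relate.** 50 × (1 − 0.20) = 40, and conversely 40 / (1 − 0.20) = 50. Forty is exactly the number left from 50 after 20% loss. That suggests a completer figure mislabelled as recruited, but it is only an inference, because the Protocol nowhere states a completer target.

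**3. Expected completers**, taking a drop-out to mean no week-8 assessment:

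- 50 recruited: 50 × 0.8 = 40, or 20 per arm.
- 40 recruited: 40 × 0.8 = 32, or 16 per arm.

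**4. Lowest count that passes the retention criterion.** This is the smallest whole number strictly above 0.65n.

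- n = 25: 0.65 × 25 = 16.25, so 17 of 25 (68%).
- n = 20: 0.65 × 20 = 13, so 14 of 20 (70%).

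**5. Chance that an arm passes if true retention is 80%** (exact binomial):

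- n = 25: P(X ≥ 17) = 0.953.
- n = 20: P(X ≥ 14) = 0.913.

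The chance that such an arm fails is therefore about 5% with 25 and about 9% with 20.

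**6. Precision at 65% retention** (normal approximation, 95% half-width):

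- n = 25: 1.96 × √(0.65 × 0.35 / 25) = 0.187, or 18.7 points.
- n = 20: 1.96 × √(0.65 × 0.35 / 20) = 0.209, or 20.9 points.

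| | 50 recruited | 40 recruited |
| --- | --- | --- |
| Per arm | 25 | 20 |
| Expected completers, total | 40 | 32 |
| Lowest passing count per arm | 17 (68%) | 14 (70%) |
| Chance an arm passes at 80% retention | 0.953 | 0.913 |
| 95% half-width at 65% retention | 18.7 points | 20.9 points |

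**The case against.** The best defence is that this is one stray word. The dedicated sample-size section gives 50, the section headed for the number of participants gives 50, and the sentence in section 4 itself carries a bracketed 50 that may be an inserted correction. Staff reading section 4 would meet 50 in the next line. The retention rule is a proportion, so its threshold stays at 65% whatever the target, and only whole-number rounding moves the pass mark, from 68% to 70%.

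Much of this stands. It shows that 50 is very probably the intended target and that the numerical effect on the criterion is small. It does not remove the conflict. If the bracketed 50 is a citation, entry 50 in the reference list is the WHODAS 2.0 page, which has no bearing on sample size. If it is a correction, the superseded word was left in.

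Two stronger readings are tempting, and the Protocol does not support them.

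- A reader might infer that 20% drop-out and the 65% retention figure contradict each other, since both cite reference 49. They do not. The first is what the sponsor expects, and the second is the minimum for declaring feasibility. A minimum below the expected rate is ordinary, and an arm of 25 with 80% true retention would pass with probability 0.953. The two may not even measure the same event: section 9.1 asks people withdrawn from the intervention to complete the post-measures where possible.
- A reader might also infer that the planned size is left open. It is not, because section 11.3 fixes 50, about 25 per arm, with 20% loss. The fault is that section 4 contradicts it.

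**Conclusion.** The contradiction is real and confined to section 4: forty recruited there, 50 in sections 4.1 and 11.3. Acting on the lower figure would mean 10 fewer participants and, at the stated drop-out, 8 fewer expected completers (32 instead of 40). The effect on the retention criterion is modest: 14 of 20 instead of 17 of 25 to pass, and a half-width wider by 2.2 points (20.9 − 18.7).

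These figures assume equal arms and, for the completer counts, that every drop-out lacks a week-8 assessment. The pass probabilities also assume independent participants with true retention of 80%. The existence of the contradiction depends on none of these assumptions. It should be corrected because a recruitment number in operative text ought to agree with the sample-size section, and correcting it is easy.

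**What to change.** In section 4, replace the forty and its bracketed 50 with 50 participants, about 25 per arm, so that the sentence agrees with sections 4.1 and 11.3. If forty was meant as the number expected to complete at 20% drop-out (50 × 0.8), the sponsor should confirm this and label it as expected completers, not as the number recruited. If the bracketed 50 was meant as a citation, remove it or point it to a source that bears on the sample size.

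The retention criterion and the drop-out assumption need no change. The cost is one sentence: no extra participants, and no change to the design or analysis.

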## Number of participants

The study will consist of a total of 50 participants.

## 4.2 Inclusion Criteria

Patients will be invited to participate in the study if they meet all of the following criteria:

1. Aged between 18-64 years (inclusive)
2. Fulfil the DSM 5 criteria for schizophrenia and related psychotic disorders (any psychotic spectrum disorder such as schizophrenia, schizoaffective disorder, bipolar disorder with psychotic features, major depressive disorders with psychosis) as confirmed by the treating psychiatrist of the unit.
3. Have a treatment plan such that they are likely to reside within the CCU for the duration of the 8-week study
4. Agree to participate, has capacity to consent and able to follow the study instructions and procedures.
5. Has been cleared to participate in an exercise program by the accredited exercise physiologist (AEP) within the service, following standard assessment of suitability and risk as per AEP exercise guidelines within the CCU’s.

Any participant deemed at risk of injury or considered medically unfit will be advised to be reviewed by their General Practitioner (G.P) and written clearance provided by the G.P before participation will be allowed in the research program (also in accordance with current policy at each CCU to allow access to the existing exercise program).

## 4.3 Exclusion Criteria

Potential participants will be excluded if:

1. They are pregnant
2. They have a comorbid eating disorder in which exercise is considered to be contraindicated by the treating psychiatrist of the unit (ie anorexia nervosa where BMI <18; presence of medical complications of an eating disorder; or anorexia or bulimia nervosa is comorbid with exercise addiction)
3. Substance abuse is considered to be interfering with rehabilitation engagement, and their ongoing suitability for rehabilitation is under review by the treating team.
4. Inability to follow the study instructions and procedures

